### Safety and ethics

The study protocol will be approved by each institution’s research ethics board and informed consent form will be obtained from enrolled patients. This study will be conducted according to the Declaration of Helsinki, Good Clinical Practice and the TriCouncil Policy.

### Sample size

Typically, sample sizes for economic analyses are based upon practical and logistic reasons with limited focus on inferential statistics [16]. Within this study, incremental costs will be estimated through regression analysis, which will incorporate a significant number of covariates to adjust for the nonrandom nature of treatment allocation. Based on traditional sample size calculations for regression analysis, a sample size of 250 will be sufficient to control for a large number of coefficients (at least 25) and give a suitable degree of precision around our primary outcome [17]. For example, if the coefficient of variation for costs was 25%, there would be sufficient power to detect a reduction in costs by 10%.

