## Methods/Design

### Design

CTA-HF is a multicenter, multinational, randomized controlled trial that is currently recruiting 250 patients from 15 sites across Canada and Finland (see Additional file 1) over 4 years, randomized to CTA versus ICA (n = 125 per group) as the first test to define coronary anatomy in patients with heart failure. This research study has approval from each participating center’s institutional research ethics board.

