### Randomization

Randomization will be coordinated by the University of Ottawa Heart Institute (UOHI) Cardiovascular Research Methods Centre. Eligible, consenting patients will be randomized to either the CTA or ICA arm and stratified according to recruitment site. A stratified block (varying sizes) randomization scheme will be used. Within each stratum, patients will be randomized with varying block sizes into the two study groups. A central randomization scheme, ensuring concealment, will be used and the site coordinator will perform patient assignments. The randomization scheme will be generated by the study statistician using a SAS (SAS Institute, Cary, North Carolina, USA) macro.

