### Secondary analysis

Secondary analysis will investigate CCE and MACE, analyzed using survival analysis techniques between the ICA and CTA arms. The survival experience (that is, time-to-major adverse cardiac event) in each of the two arms will be summarized using Kaplan-Meier product limit estimates and the log-rank test will be used for comparing the survival curves. The hazard ratio with 95% confidence interval (CI) will be calculated. To adjust for possible effects of covariates on survival, the Cox’s proportional hazards model will be used. Underlying assumptions for these statistical procedures will be assessed; in particular, the proportional hazard assumption will be assessed using graphical and numerical tests, and stratified Cox models or Aalen’s additive model will be considered as needed.

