#### Costs associated with the use of computed tomographic coronary angiography

The incremental cost associated with the management algorithm that includes the use of CTA will be estimated as follows. A data set will be constructed containing the total costs per patient. For each observation the patient will be assigned a dummy variable relating to whether they were assigned to the management algorithm or to standard care. Regression will be conducted using appropriate generalized linear models controlling for all potential covariates. The appropriate coefficient from the regression will represent the incremental cost associated with the use of CTA.

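### The primary cost regression is justified by a nonrandom allocation that this randomised trial does not have, and its covariate rule is not limited to baseline variables

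*Protocol article*

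**What the plan says.** The Design section describes patients "randomized to CTA versus ICA (n = 125 per group) as the first test to define coronary anatomy in patients with heart failure". The Randomization section says they are "randomized to either the CTA or ICA arm and stratified according to recruitment site", with varying block sizes, and adds: "A central randomization scheme, ensuring concealment, will be used and the site coordinator will perform patient assignments".

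The Sample size section gives a different picture. Incremental cost will come from a regression that will "incorporate a significant number of covariates to adjust for the nonrandom nature of treatment allocation", and 250 patients are said to leave room for 25 or more coefficients.

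The section on costs associated with CTA defines the model. Each patient gets a dummy variable for the assigned strategy. On covariates the rule is: "Regression will be conducted using appropriate generalized linear models controlling for all potential covariates". The fitted arm coefficient is then read as the extra cost of using CTA. The Outcome measures and Primary analysis sections make that incremental cost the primary result.

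The Data analysis section makes the primary population intention-to-treat. For clinical events, the Secondary analysis section says that "the log-rank test will be used for comparing the survival curves", with covariate-adjusted Cox models, and stratified Cox models if assumptions fail.

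**The concern.** The reason given for adjusting decides what the adjustment is for. In a randomised trial the arms are comparable in expectation, and baseline covariates are added for precision. If allocation were nonrandom, covariates would be needed to remove bias, the unadjusted comparison would be suspect, and adding more variables would look safer. An analysis plan that followed the Sample size section would inherit the second logic for a trial that needs the first.

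The open covariate rule makes this matter more. The Hypotheses section says that the saving arises because CTA reduces later use of resources. Later ICA, further tests and hospitalisations are recorded in the database that feeds the cost model. They are strong predictors of cost, and they are also how the strategy changes cost. A rule that admits every potential covariate does not keep them out. Conditioning on one of them would remove part of the effect that the trial sets out to measure.

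**Working it through.** **1. The two accounts of allocation.** Design and Randomization describe chance assignment with 125 per group, concealed and stratified. Sample size describes allocation that needs correcting. The clause cannot sensibly refer to crossover after randomisation, because the arm variable is the assigned strategy and the primary population is intention-to-treat. The accounts do not reconcile, and the Sample size clause is the wrong one.

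**2. The plan's own power statement.** Inputs from the Sample size section are a coefficient of variation of 25% and a 10% reduction, with 125 per arm. No alpha or target power is given; I assume two-sided 5%.

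- Standard error = 0.25 × √(2/125) = 0.0316.
- 0.10/0.0316 = 3.16, and 3.16 − 1.96 = 1.20, so power is 88.5% (93.5% one-sided).
- Total N is 198 for 80% power and 264 for 90%.

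The claim of sufficient power at 250 is therefore consistent with its own inputs. With 25 uninformative baseline covariates, chance correlation with arm inflates the variance by about 249/(249 − 25) = 1.11, and power is about 85%. The number of baseline covariates is not the problem.

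**3. What a post-randomisation covariate would do.** Let c be the cost of CTA and k the cost of ICA; the document gives neither. From Outcome measures, 50/125 = 40% of the CTA arm goes on to ICA. Assume that every ICA-arm patient has ICA.

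- Testing cost in the CTA arm: c + 0.4k.
- Testing cost in the ICA arm: k.
- Effect by assignment: c + 0.4k − k = c − 0.6k.

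Now add receipt of ICA to an additive model. Only three groups exist: CTA arm with ICA, CTA arm without ICA, and ICA arm with ICA. The arm coefficient is then the contrast of the first with the third. Let m₁ and m be the mean other costs in those two groups:

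(c + k + m₁) − (k + m) = c + (m₁ − m).

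With no selection in other costs (m₁ = m) this is +c. The sign then reverses whenever 0 < c < 0.6k.

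**4. Numerical check.** Least-squares simulation, 2,000 runs, 125 per arm, arbitrary units, other costs about 8. A baseline severity variable drives both later ICA and other costs, and it is in the model for the last two columns.

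| c, k (assumed) | c − 0.6k | Unadjusted | Baseline covariate | Baseline + ICA receipt |
|---|---|---|---|---|
| 0.5, 2 | −0.70 | −0.70 | −0.70 | +0.52 |
| 0.4, 2 | −0.80 | −0.80 | −0.81 | +0.41 |
| 0.6, 3 | −1.20 | −1.19 | −1.20 | +0.62 |
| 1, 2 | −0.20 | −0.21 | −0.21 | +1.00 |

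Baseline adjustment leaves the effect where it was. Adding ICA receipt replaces it with approximately the price of CTA.

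**The case against.** The best defence is that the document does not plan a harmful analysis. It names no post-randomisation covariate. It places initial imaging, later ICA and hospitalisation among the resources that make up total cost, so they belong to the outcome. The patient characteristics that it lists, in Data analysis, are baseline ones. The arm variable is as assigned and the primary population is intention-to-treat. A full covariate list is ordinary analysis-plan content, and the article need not give one. All of this stands, and it limits the point to a false rationale and a rule worded too widely.

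A reader might infer more in three ways.

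- *That the plan will reverse the cost effect.* The text permits such a model but does not describe it. The figure of +c also needs full ICA receipt in the ICA arm, an additive model, and equal other costs in the groups compared. CTA patients sent on to ICA are selected by their scan, so m₁ may differ from m. The GLM link is left open as well.
- *That the primary test is inflated by covariate selection.* In an illustrative null simulation (1,000 runs), reporting the best of 22 covariate sets gave 16.5% type I error, against 5.1% with all 25 pre-specified and 4.1% unadjusted. No such selection appears in the document; its wording, read literally, means including every covariate.
- *That the log-rank test is invalid because site is not mentioned.* Ignoring a stratification factor there is at most slightly conservative, and site could fall within the open covariate rule of the cost model.

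**Conclusion.** The Sample size section misdescribes the design, and the misdescription is the stated reason for the model that yields the primary result. That is an error on the page, not a detail left to the analysis plan. Combined with a covariate rule that has no baseline limit, it leaves room for a model whose arm coefficient would not estimate the cost effect of the strategy.

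The size of that risk is conditional. Under the assumptions shown, c − 0.6k would become about +c; outside them the coefficient would be c plus an unknown selection term. Only the 40% comes from the document, and the prices are assumed. Adjustment for many pre-specified baseline covariates would not in itself bias the estimate, and the power statement is not at fault on its own inputs. The point should be fixed. It does not show that the planned analysis is biased.

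**What to change.** In Sample size, delete the clause on nonrandom allocation and state that covariates are used for precision. In the costing section, replace the open rule with a short list of baseline covariates, fixed before outcome data are examined, plus recruitment site. With 250 patients over 15 sites (250/15, about 17 each on average), small sites should be pooled by a rule set in advance. State that no variable arising after randomisation enters the primary model. Report the unadjusted arm difference beside the adjusted one.

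A minor improvement at no cost is to stratify the log-rank and Cox analyses by the same pooled site factor.

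The change is to wording only, and N stays at 250. The price is less freedom to add covariates later.

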### Data analysis

For the purposes of data analysis, two study groups will be defined: ‘intention-to-treat’ (ITT) population which consists of all patients who are randomized to the CTA or ICA regardless of whether they actually receive the approach, and ‘per protocol’ population which excludes patients randomized but not receiving the allocated approach. Primary analyses will be conducted on the ITT population, and the sensitivity analyses will be conducted on the per-protocol population. Descriptive statistics for the baseline demographic characteristics will be summarized for the study group by means of frequency for categorical variables and mean, standard deviation, median and interquartile ranges for continuous variables. Demographic information includes age, comorbidities, cardiac history, cardiac risk factors and medications. Groups will be compared on continuous variables using Wilcoxon rank-sum tests and on categorical variables using Fisher’s exact tests.

### Primary analysis

Primary analysis will estimate average health care costs per patient for CTA versus ICA. Resource utilization will be measured as detailed below. Cost is defined as the incremental cost of the diagnostic strategy using CTA and will represent the primary outcome measure. Cost will be estimated through regression methods detailed below. Thus, estimations of incremental cost will be evaluated based on costing the components of care.

### Secondary analysis

Secondary analysis will investigate CCE and MACE, analyzed using survival analysis techniques between the ICA and CTA arms. The survival experience (that is, time-to-major adverse cardiac event) in each of the two arms will be summarized using Kaplan-Meier product limit estimates and the log-rank test will be used for comparing the survival curves. The hazard ratio with 95% confidence interval (CI) will be calculated. To adjust for possible effects of covariates on survival, the Cox’s proportional hazards model will be used. Underlying assumptions for these statistical procedures will be assessed; in particular, the proportional hazard assumption will be assessed using graphical and numerical tests, and stratified Cox models or Aalen’s additive model will be considered as needed.

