### Hypotheses

The primary hypothesis is that, compared to ICA, a diagnostic strategy algorithm using CTA for HF patients will result in a reduction in downstream resource utilization leading to a reduction in average costs per patient.

The first of two secondary hypotheses states that compared to ICA (standard of care), a CTA strategy will achieve: a) similar composite clinical events (CCE) (cardiac death, myocardial infarction (MI), resuscitated cardiac arrest and cardiac re-hospitalization (worsening heart failure, acute coronary syndrome arrhythmia), QoL, and MACE (cardiac death, non-fatal MI); b) a lower rate of procedure related complications (death, MI, stroke, vascular complications, severe allergic reactions; contrast nephropathy); and c) a lower rate of normal ICA. The second of the two secondary hypotheses states that using patient-based analysis and vessel-based analysis, CTA has very good agreement with ICA among patients with HF in the CTA arm who proceed to ICA.

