### Outcome measures

The primary outcome (average health care costs per patient) will be determined through regression methods detailed below.

All secondary outcome measures will be determined: (CCE (cardiac death, myocardial infarction, resuscitated cardiac arrest and cardiac re-hospitalization (worsening heart failure, acute coronary syndrome arrhythmia), QoL, procedural complications (all-cause death, myocardial infarction, stroke, vascular complications, severe allergic reactions; contrast nephropathy), and rate of normal ICA.

CTA accuracy: To address the 2^nd^ secondary hypothesis, regarding CTA accuracy, the accuracy in the cohort of patients randomized to CTA and undergoing subsequent ICA (sensitivity, specificity, predictive values and likelihood ratios) will be determined and reported with 95% confidence intervals (CI). It is estimated that 50/125 of the patients randomized to CTA will have subsequent ICA, which will enable the comparison of CTA accuracy to ICA.

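### Kaplan-Meier curves for CCE and MACE must censor non-cardiac deaths, so they overstate the event probability in any arm where such deaths occur; cumulative incidence curves should replace them

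*Protocol article*

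**What the plan says.** The Hypotheses section states the first secondary hypothesis as "similar composite clinical events (CCE) (cardiac death, myocardial infarction (MI), resuscitated cardiac arrest and cardiac re-hospitalization" and so on. The only death in this composite is cardiac. The same section gives "MACE (cardiac death, non-fatal MI" as the content of MACE, again with cardiac death only. The Outcome measures section repeats the restriction for CCE: "CCE (cardiac death, myocardial infarction, resuscitated cardiac arrest and cardiac re-hospitalization". All-cause death is named in one place only, the safety outcome of "procedural complications (all-cause death, myocardial infarction, stroke, vascular complications, severe allergic reactions; contrast nephropathy".

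The Secondary analysis section sets the method: "Secondary analysis will investigate CCE and MACE, analyzed using survival analysis techniques between the ICA and CTA arms". The curve in each arm is to be "summarized using Kaplan-Meier product limit estimates and the log-rank test will be used for comparing the survival curves". It adds: "The hazard ratio with 95% confidence interval (CI) will be calculated". A Cox model is planned for covariate adjustment. If proportional hazards fails, "stratified Cox models or Aalen’s additive model will be considered as needed".

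The article does not mention competing risks or cumulative incidence, and it does not say how a non-cardiac death is handled. The Frequency and duration of follow-up section gives a mean of 3 years and a range of 2 to 4 years.

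**The concern.** A patient who dies of a non-cardiac cause before any component event can no longer have a CCE or a MACE. Kaplan-Meier censors that patient, and so assumes that the risk from then on matches that of patients still under observation. One minus Kaplan-Meier therefore estimates the event probability in a hypothetical population without non-cardiac death. It lies above the proportion of patients who actually have the event, and the gap widens with follow-up.

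This is not a detail left for the analysis plan to fill in. The article names the per-arm summary, and that summary does not suit the endpoints that the article defines. The fallback models do not help, because they are offered for the proportional hazards assumption and do not deal with competing death.

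At stake is the reading of the per-arm curves. The trial expects CCE and MACE to be similar between strategies, and the Cost analysis section plans a cost minimization, which rests on comparable outcomes. Readers may well take event probabilities off the published curves when they judge this.

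**Working it through.** **No stated figure to reproduce.** The article gives no event rate, event count or power for CCE or MACE. Its only quantitative design statement concerns costs. Every rate below is an assumption.

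**Inputs from the article:** cardiac death only in CCE and MACE (Hypotheses; Outcome measures for CCE); Kaplan-Meier per arm (Secondary analysis); follow-up mean 3 years, maximum 4; 125 patients per arm (Design).

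**Assumed inputs:** constant composite hazard h = 0.05, 0.10 or 0.20 per year; constant non-cardiac death hazard c = 0.02, 0.04 or 0.06 per year.

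**Formulas:**
- One minus Kaplan-Meier, non-cardiac death censored: 1 − exp(−h·t)
- Actual cumulative incidence (the target of Aalen-Johansen): h/(h + c) × [1 − exp(−(h + c)·t)]

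**Worked example,** h = 0.10, c = 0.06, t = 3:
- Kaplan-Meier: 1 − exp(−0.30) = 25.9%
- Cumulative incidence: (0.10/0.16) × [1 − exp(−0.48)] = 0.625 × 0.3812 = 23.8%
- Excess: 2.1 points

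**Results** (excess in percentage points for c = 0.02 / 0.04 / 0.06):

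| h per year | t (years) | 1 − KM | Cumulative incidence | Excess |
|---|---|---|---|---|
| 0.05 | 3 | 13.9% | 13.5 / 13.1 / 12.8% | 0.4 / 0.8 / 1.2 |
| 0.10 | 3 | 25.9% | 25.2 / 24.5 / 23.8% | 0.7 / 1.4 / 2.1 |
| 0.20 | 3 | 45.1% | 43.9 / 42.8 / 41.7% | 1.2 / 2.3 / 3.5 |
| 0.05 | 4 | 18.1% | 17.4 / 16.8 / 16.2% | 0.7 / 1.3 / 1.9 |
| 0.10 | 4 | 33.0% | 31.8 / 30.6 / 29.5% | 1.2 / 2.3 / 3.4 |
| 0.20 | 4 | 55.1% | 53.2 / 51.4 / 49.7% | 1.9 / 3.6 / 5.3 |

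With c = 0 the two formulas coincide and the excess is zero. With lower assumed rates (h = 0.03, c = 0.005, t = 2) it is only 0.03 points.

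**Simulation check.** With 400,000 patients and administrative censoring uniform over 2 to 4 years, the 3-year values were 13.9% against 13.5% (h = 0.05, c = 0.02) and 45.2% against 44.0% (h = 0.20, c = 0.02). Both agree with the formulas.

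**Between-arm contrast.** Take h = 0.12 in one arm and 0.10 in the other, with the same c in both, at 4 years. Kaplan-Meier gives 38.1% − 33.0%, a difference of 5.2 points before rounding. Cumulative incidence gives 5.0 points for c = 0.02 and 4.7 for c = 0.06. The difference shifts by 0.2 to 0.5 points. With equal h and equal c in both arms, the bias in the difference is exactly zero.

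**Sampling error for scale.** With 125 per arm, the binomial standard error of one arm's 3-year risk is √(0.139 × 0.861/125) = 3.1 points at 13.9% and √(0.259 × 0.741/125) = 3.9 points at 25.9%. The 95% half-width for a difference is 1.96 × √2 times that, about 9 to 11 points.

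**The case against.** The strongest reply is that the section promises survival curves, a log-rank test and a hazard ratio, but no landmark risk and no risk difference. The planned comparative tools stay valid as comparisons of cause-specific hazards. Allocation is randomized and concealed, and the arms differ only in the first diagnostic test, so non-cardiac mortality should be similar and the bias should nearly cancel. The per-arm excess is mostly smaller than the sampling error of one arm. The endpoints are secondary. The article is condensed and never writes out that non-cardiac deaths are censored.

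Most of this stands, and it limits the point. A reader might infer that the planned comparison of CTA with ICA is itself invalid, or that a risk difference the plan relies on is materially wrong. The documents do not support either reading: no risk difference is promised, and log-rank and Cox remain interpretable. Nor do they show that non-cardiac mortality will differ by arm. The procedural risks that the Background quotes for ICA are low (death 0.12%), so a differential from that source is probably small.

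Two parts of the reply fail. Censoring is not written out, but it follows from the definitions and the named estimator, because Kaplan-Meier has no other way to treat a death that is not an event. And a bias smaller than the sampling error is still a bias in a known direction, which a standard estimator removes.

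**Conclusion.** The point holds for the per-arm curves. One minus Kaplan-Meier overstates the probability of CCE and MACE in any arm where patients die of non-cardiac causes while still free of the event and others go on to have it. The direction is certain given the definitions. The size cannot be fixed from the documents. Under the assumed constant hazards it is modest at the 3-year mean follow-up, and the largest value in the table needs the highest assumed rates and the 4-year maximum. It would be wrong to say that the curves will be materially inflated in both arms whatever happens: with few non-cardiac deaths the excess is negligible.

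Neither the between-arm hazard comparisons nor the primary cost estimate is in question.

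**What to change.** In the Secondary analysis section, replace the Kaplan-Meier summary of CCE and MACE with Aalen-Johansen cumulative incidence curves for each arm, treating non-cardiac death as a competing event. Keep the log-rank test, hazard ratio and Cox model, and state that they compare cause-specific hazards.

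The cost is a change of wording and a little standard code, with no effect on conduct or sample size. Deaths must be classified as cardiac or non-cardiac, which the endpoint definitions already require. The Study management section has a blinded committee adjudicating each clinical event; that this covers cause of death is a reasonable inference, but the article does not say so, and it should be confirmed.

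A composite with all-cause death in place of cardiac death could be added as a sensitivity analysis. It is a different endpoint and is optional.
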